## Abstract

**Background:**

In the presence of type 2 diabetes (T2DM) or coronary heart disease (CHD), depression is under diagnosed and under treated despite being associated with worse clinical outcomes. Our earlier pilot study demonstrated that it was feasible, acceptable and affordable for practice nurses to extend their role to include screening for and monitoring of depression alongside biological and lifestyle risk factors. The current study will compare the clinical outcomes of our model of practice nurse-led collaborative care with usual care for patients with depression and T2DM or CHD.

**Methods:**

This is a cluster-randomised intervention trial. Eighteen general practices from regional and metropolitan areas agreed to join this study, and were allocated randomly to an intervention or control group. We aim to recruit 50 patients with co-morbid depression and diabetes or heart disease from each of these practices. In the intervention group, practice nurses (PNs) will be trained for their enhanced roles in this nurse-led collaborative care study. Patients will be invited to attend a practice nurse consultation every 3 months prior to seeing their usual general practitioner. The PN will assess psychological, physiological and lifestyle parameters then work with the patient to set management goals. The outcome of this assessment will form the basis of a GP Management Plan document. In the control group, the patients will continue to receive their usual care for the first six months of the study before the PNs undergo the training and switch to the intervention protocol. The primary clinical outcome will be a reduction in the depression score. The study will also measure the impact on physiological measures, quality of life and on patient attitude to health care delivered by practice nurses.

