### Objectives of this study

The primary objective of this study is to determine whether practice nurse-led collaborative care is better than the usual method of GP-led episodic care for the management of co-morbid depression in patients with heart disease or diabetes by testing whether there is an improvement in the depression score at the end of the study. The goal is to achieve a 50% reduction in that score. It will also test whether it is a practical way to manage this complex and increasing chronic-disease burden. It will introduce an hour-long consultation with the practice nurse in which patient goal setting forms an important proactive part of the patient care. One key strategy is that the patient outcomes will be reviewed every three months over an entire year and patient goals altered accordingly. Other objectives are to demonstrate that the model of care can use existing clinical staff and be funded within current Medicare arrangements, and that it can be used in large and small practices across rural and urban settings.

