#### Randomisation

Nine practices were randomly allocated to the intervention group in which nurse-led collaborative care will be undertaken. The remaining nine practices were allocated to the control group in which the usual GP-led care will continue for a period of six months. At the end of this period, the control practices will be invited to implement the practice nurse-led model of collaborative care and to send practice nurses to a training workshop (see below).

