### Patient recruitment

Within each general practice, a mailing list of patients with a diagnosis of CHD or T2DM is generated. Patients who are either under 18 years of age or in residential care are excluded from the study. Eligible patients are added to the master list as potential participants in the programme and assigned a unique identification (ID) number. All documentation or data forwarded to the researchers for the patient is identified only by this unique ID number. Personal details of patients, including names and addresses, are retained by the clinic concerned.

An information package is posted from the practice to each of these patients. It includes a standardised personal letter from their GP explaining the study, information brochures, a PHQ-9 questionnaire, and a consent form indicating the patient's willingness to participate in the programme. Each patient is asked to complete and return the PHQ-9 and consent forms. The returned PHQ-9 questionnaire from consenting patients is examined to identify PHQ-9 scores above 5, indicating presence of at least mild depression. These patients are invited to join the study. Patients who do not respond to the first mail-out are sent a reminder letter approximately two weeks later inviting them to participate, with further reminder letters, telephone calls and personal invitations when visiting clinics, until 50 patients have been recruited.

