An important aspect of this collaborative care programme is that patients are recalled systematically to monitor the progress of their care. Another important aim is that the nurse-led care can be completely self-funded using the normal Medicare item numbers. Consequently, a thirteen-week interval was chosen as the recall period. The recall visits are booked at the time of the previous visit. During each review, patients will complete a new PHQ-9 questionnaire so that any changes to their mental health can be monitored. Additional therapies or new strategies can be considered during the consultations if the PHQ-9 score has not improved by at least 50% or dropped below 5. These strategies may include changing or adding medication or referral to a mental health professional. The PN and patient then re-evaluate the goals from the previous consultation. In the second (6-month) and fourth (12-month) consultations, the patient will complete a new SF36v2 form to assess changes in quality of life.

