## Discussion

The strength of this programme is that it provides a full package of chronic disease management techniques, based on Wagner's chronic disease management (CDM) model [19]. The programme involves reading the practice electronic medical record to generate a master list of patients who satisfy the prescribed selection criteria. These patients are invited to begin the collaborative care process, and are systematically recalled at the prescribed review period. The collaborative care process is audited using patient feedback. Medicare funding will mean practices are remunerated for the more intense patient intervention.

The programme uses the existing workforce but involves an enhanced role for the practice nurses and so is applicable for wider roll out in using this potentially under-utilised resource. The practice nurses gain enhanced skills in the CDM set up and management that will be a useful model for patients with other chronic diseases.

A full range of outcome measures is reported and added to the electronic database. Consequently, practices will know what happens to patients (process of care) and will be able to identify changes in classic risk factors, depression symptoms and affordability within the Australian health system.

We note that practices need to be large enough to have available a practice nurse to participate in the programme. This study is only funded for 15 months of data collection but early feedback from participating practices indicates they are likely to choose to continue this nurse-led collaborative model of care beyond the lifetime of the research.

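### The six-month usual-care period in control practices is not tied to patients' baselines or to the end of recruitment, so late-recruited controls may be exposed early or followed for less time

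*Protocol article*

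**What the plan says.** Four parts of the protocol article bear on the timing.

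- **Control period.** The abstract (Methods) states that "the patients will continue to receive their usual care for the first six months of the study before the PNs undergo the training". The Randomisation section describes "the control group in which the usual GP-led care will continue for a period of six months" and gives no starting point.
- **Switch.** It happens by practice, through nurse training: "At the end of this period, the control practices will be invited to implement the practice nurse-led model of collaborative care".
- **Recruitment.** The Patient recruitment section describes a mail-out, a reminder about two weeks later, and then more letters, "telephone calls and personal invitations when visiting clinics, until 50 patients have been recruited". No closing date is given.
- **Outcome timing.** The Intervention programme section sets recalls 13 weeks apart and repeats the SF-36 "In the second (6-month) and fourth (12-month) consultations", counted from the patient's first session. The Objectives section places the primary test elsewhere: "testing whether there is an improvement in the depression score at the end of the study".

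**The concern.** Two clocks are in use. Visits run on patient time. The only stated start for the control period is on study time, and that period ends with an event that affects a whole practice at once. A nurse workshop cannot fall at the personal six-month point of 50 patients who entered on different dates.

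Six months is the latest point at which a usual-care arm is planned, so the cleanest randomised contrast depends on it. Two things can go wrong for a control patient who enters late:

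- If the outcome is taken six months after that patient's baseline, part of the follow-up may lie after the switch, which pulls the contrast towards zero.
- If the outcome is taken at study month six, the patient has been followed for less time than an intervention patient at the six-month visit.

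Either way the arms are not compared after equal time on their allocated care. Moving the primary comparison from the end of the study to six months would not cure this. The analysis cannot undo exposure that has already happened, so the decision belongs in the conduct of the trial, before the control workshop.

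**Working it through.** **Inputs.** From the Sample size section: difference 2 points, SD of change 5.1, significance level 0.05, power 80%, ICC 0.04, drop-out 33%, 9 practices of 50 per arm (450). Two-sided testing is assumed because the article does not say. Recruitment length is not given.

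**Step 1: reproduce the plan's figure.**

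- n per arm without clustering = 2 × (5.1 × (1.960 + 0.842) / 2)² = 102.1.
- Design effect = 1 + (50 − 1) × 0.04 = 2.96, giving 102.1 × 2.96 = 302.1.
- Drop-out: 302.1 / 0.67 = 451 per arm, or 9.02 practices of 50.

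This matches the stated 450. Power at 450 per arm is found as follows:

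- Effective n = 450 × 0.67 / 2.96 = 101.9.
- SE = 5.1 × √(2 / 101.9) = 0.715.
- Power = Φ(2 / 0.715 − 1.960) = 79.9%.

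If the design effect is applied to completers (33.5 per practice), it is 1 + 32.5 × 0.04 = 2.30. Effective n is then 131.1, SE 0.630 and power 88.8%. Both versions assume the full 2-point contrast.

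**Step 2: what a study-time switch does to a late entrant.** A control patient who enters at study month t has 6 − t months of usual care before a switch at month 6. A patient-time six-month outcome then falls t months after the switch.

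**Step 3: illustrative size.** None of these assumptions is in the documents: entry uniform over R months, all control practices taking up the model at month 6, outcome six months after each baseline, and effect proportional to exposed time. The mean exposed fraction is (R/2)/6 = R/12, so the contrast is 2 × (1 − R/12). Power is Φ(contrast / SE − 1.960).

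| R (months) | Usual care, last entrant (6 − R) | Contrast | Power, design effect 2.96 | Power, design effect 2.30 |
|---|---|---|---|---|
| 0 | 6 | 2.00 | 80% | 89% |
| 1 | 5 | 1.83 | 73% | 83% |
| 2 | 4 | 1.67 | 65% | 75% |
| 3 | 3 | 1.50 | 56% | 66% |

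If slow start-up after the switch realises only half of the exposure at R = 3, the contrast is 2 × (1 − 0.125) = 1.75. Power is then Φ(1.75 / 0.715 − 1.960), about 69% with design effect 2.96.

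**Step 4: the other reading.** If controls are instead assessed at study month 6, there is no exposure, but their mean follow-up is 6 − R/2 months: 5.5, 5.0 or 4.5 for R = 1, 2 or 3. Intervention patients have 6 months at their six-month visit.

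**The case against.** The strongest reply is that this is an ambiguity in a condensed article.

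- **Start of the clock.** The study-time wording is in the abstract only. The Randomisation section leaves the start open, which would fit a clock that begins at patient baseline or after recruitment. The flowchart is not shown. This stands against any claim that the switch certainly comes too early. It does not remove the problem: the one start that is stated uses study time. Even a period counted from each baseline does not by itself protect late entrants when the nurses of a whole practice are trained together.
- **Control outcome at six months.** This is inferred. The 6- and 12-month consultations are described for the intervention programme, and the primary objective refers to the end of the study. This also stands. If the end of the study means 12 months, however, exposure could reach every control patient, not only late ones.
- **Uptake.** Practices are only invited to switch. Nurses must then attend a workshop and book one-hour sessions, so a control patient shortly past the switch may have had one session or none. If the first session after the switch includes a new PHQ-9 and SF-36, it might even supply a largely unexposed measurement. This stands as a reason to expect less dilution than the table shows, although the article does not say that such a measurement will be used.

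A reader might also infer that recruitment is bound to be slow, from the pilot's patient numbers, or that it conflicts with the statement that "This study is only funded for 15 months of data collection". The documents support neither. The article gives no recruitment period for the pilot. Twelve months of review plus three months of entry fits 15 months exactly, and nothing says that entry takes longer.

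**Conclusion.** The point holds as a gap in the design. The article does not anchor the control period to patients' baselines or to the end of recruitment, and it does not fix the primary comparison at or before the switch. Followed as written, the plan may expose late-recruited controls early or give the arms unequal follow-up.

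It would go too far to say that late controls will receive the intervention before their outcome. That needs the abstract's wording to govern, a control outcome on patient time, entry spread over time and prompt uptake. The last three are not stated as facts in the article.

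The size cannot be computed from the documents, because recruitment length is missing. The contrasts of 1.83 to 1.50 points, and power of 73% to 56% (83% to 66% with the design effect on completers), are conditional on the assumptions in the working. Slower or incomplete uptake gives smaller losses.

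**What to change.** Reconcile the abstract with the Objectives, Randomisation, Patient recruitment and Intervention programme sections:

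1. Define the control period as six months from each patient's baseline, and name the time point of the primary comparison so that it falls at or before the switch.
2. Set one recruitment closing date for both arms.
3. Hold each control practice's workshop and switch until its last recruited patient has completed the six-month PHQ-9 and SF-36. If entry closed at study month 3, for example, the switch would fall at about month 9 (3 + 6).

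If the workshop date cannot move, collect a PHQ-9 from every control patient just before it and compare with intervention patients at the same elapsed time since baseline. Intervention patients are measured every 13 weeks, so this needs either matched extra measurements or actual time since baseline in the mixed model.

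The cost is protocol wording and a later workshop. Control practices may wait up to about three months longer, and a closing date may leave some practices below 50 patients.

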**Conclusion:**

The strength of this programme is that it provides a sustainable model of chronic disease management with monitoring and self-management assistance for physiological, lifestyle and psychological risk factors for high-risk patients with co-morbid depression, diabetes or heart disease. The study will demonstrate whether nurse-led collaborative care achieves better outcomes than usual care.

## Background

Coronary heart disease (CHD) and type 2 diabetes mellitus (T2DM) are both major causes of disability. The incidence of T2DM is now reaching epidemic proportions in Australia [1] and overseas [2], particularly as the population ages and becomes more obese [3]. Within 20 years diabetes will become the leading contributor to the overall burden of disease in Australia [4] with Australian health care expenditure projected to increase to $7 billion by 2023 [5]. CHD already affects over 300,000 people in Australia and remains the most common cause of death [6]. Both diabetes and heart disease are associated with a number of serious complications, each with its own cost.

There is evidence that the presence of depression in patients with CHD or T2DM leads to increased morbidity and mortality [7,8], but co-morbid depression is often missed in routine consultations within general practices [9]. One difficulty is that the traditional model used by general practices is one in which visits to the general practitioner (GP) are initiated by patients when they feel that their needs warrant a consultation. Such visits are usually episodic and cease when the immediate symptoms are relieved. Consequently, such patients miss out on regular monitoring of their chronic disease so that risk factors go unrecognised [9].

A collaborative model is one in which the care delivery has multiple components that address these problems [10] and has been shown to have good results in treating depression [11]. It relies on a case manager to coordinate that care. Hickie and McGorry [12] summarise the planned episodes of care that include:

• Use of evidence based guidelines;

• Systematic screening and monitoring of risk factors;

• Timetabled recall visits;

• New or adjusted roles for team members;

• Information support for the clinician;

• Enhanced patient self-management;

• Identified case manager to coordinate care;

• A means of effective communication between all members of the care team; and

• Audit information for the practice.

The True Blue study described in this paper extends an exploratory trial to adapt the successful IMPACT model of collaborative care for depression in the USA [10] to an Australian primary health care setting. The case manager in this study is the practice nurse (PN). The model of practice nurse-led collaborative care was demonstrated in six general practices in rural southern Australia, with 332 patients recruited [13]. In this exploratory trial a practice nurse training programme was developed for chronic disease management, introducing depression screening and counselling techniques to assist with self-management. Electronically based multi-purpose tools were designed and tested to allow outcome data to be collected to inform coordinated medical care and patient self-management. The trial found depression in 34% of patients with CHD or T2DM, and demonstrated that the practice nurse-led, collaborative care model was both feasible and acceptable.

The role of practice nurses in collaborative care of chronic disease is being investigated both in Australia and overseas. [14-16]. The features of the True Blue study are that the programme

• routinely screens for depression;

• monitors depression severity over time for participating patients;

• uses the existing work force and funding arrangements to potentially make the model more widely applicable;

• uses consultations with practice nurses that allow collection of physiological measurements, monitoring of lifestyle and mental health risks and setting of patient goals; and

• is linked with appointments to the patient's usual general practitioner (GP).

The present study works with this subset of patients who have co-morbid depression and aims to demonstrate improved clinical outcomes for this higher-risk group through measurements of physiological, mental health and lifestyle parameters at regular intervals throughout the study period. It will further test and implement this collaborative care model that is focussed on the patient. An important aspect is that patients, in collaboration with the practice nurse, will develop up to three goals that they feel will be able to help reduce their risk factors, thus making patients active participants in their own health care.

The model is also intended to demonstrate how the care of co-morbid depression, heart disease and diabetes can be funded successfully using Australian Medicare Benefits Schedule (MBS) Item numbers. It will develop training programmes for PNs in screening, assessment and management of patients with co-morbid depression and heart disease or diabetes, and evaluate the feasibility of PNs to carry out screening and assessment.

### Objectives of this study

The primary objective of this study is to determine whether practice nurse-led collaborative care is better than the usual method of GP-led episodic care for the management of co-morbid depression in patients with heart disease or diabetes by testing whether there is an improvement in the depression score at the end of the study. The goal is to achieve a 50% reduction in that score. It will also test whether it is a practical way to manage this complex and increasing chronic-disease burden. It will introduce an hour-long consultation with the practice nurse in which patient goal setting forms an important proactive part of the patient care. One key strategy is that the patient outcomes will be reviewed every three months over an entire year and patient goals altered accordingly. Other objectives are to demonstrate that the model of care can use existing clinical staff and be funded within current Medicare arrangements, and that it can be used in large and small practices across rural and urban settings.

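### The primary test is set at the end of the study, but the control arm is on usual care for only six months, and the six-month contrast is never named as primary

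*Protocol article*

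**What the plan says.** All references are to the protocol article.

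- **Comparison.** Objectives of this study: the question is whether "practice nurse-led collaborative care is better than the usual method of GP-led episodic care".
- **Time point.** The same sentence answers it by "testing whether there is an improvement in the depression score at the end of the study". The paragraph adds that "the patient outcomes will be reviewed every three months over an entire year".
- **Length of follow-up.** Intervention programme: "In the second (6-month) and fourth (12-month) consultations, the patient will complete a new SF36v2 form". The Discussion says that data collection is funded for 15 months.
- **Control arm.** Randomisation: "the usual GP-led care will continue for a period of six months". Control practices are then invited to adopt the nurse-led model and send nurses for training. The Methods paragraph of the Abstract says control patients "continue to receive their usual care for the first six months of the study before the PNs undergo the training", and that the nurses then move to the intervention protocol.
- **Analysis.** Data collection, verification and analysis: change from baseline to an unspecified follow-up is compared between groups by a linear mixed model with group and time factors, under intention to treat. No visit is singled out, and nothing is said about control data collected after the switch.
- **Sample size.** The target is a 2-point PHQ-9 reduction, with no time point given.

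**The concern.** The stated comparator and the stated time point do not fit together. Usual care in the control arm is assured for six months only. A patient's last scheduled consultation is at 12 months, and by then the control practices have switched or been invited to. A contrast at that point estimates the effect of starting nurse-led care early rather than about six months later, which is a different question from nurse-led care versus usual care. If the intervention works and switched controls benefit, the difference shrinks, and an effective model of care could be reported as no better than usual care. Intention to treat does not help, because it keeps switched patients in the control group.

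Leaving six months unnamed has a second cost. With assessments every three months and no designated visit, the choice between a six-month and a 12-month result could be made after the data are seen.

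**Working it through.** **1. Where the arms differ in treatment**

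| Period | Intervention arm | Control arm |
|---|---|---|
| Baseline to 6 months | Nurse-led care | Usual GP care (Abstract; Randomisation) |
| After 6 months, to the 12-month visit | Nurse-led care | Switched to nurse-led care (Abstract), or invited to adopt it (Randomisation) |

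Only the first row matches the comparison in the Objectives. The end of the study falls in the second.

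**2. Reproducing the stated sample size**

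Inputs from the Sample size section: difference 2 points, SD of change 5.1, alpha 0.05, power 80%, dropout 33%, intra-cluster correlation 0.04, 9 practices per arm with 50 patients each. Two-sided alpha is my assumption, as sidedness is not stated.

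- Patients per arm without clustering: 2 × [5.1 × (1.960 + 0.842) / 2]² = 102.07, rounded up to 103.
- Design effect: 1 + (50 − 1) × 0.04 = 2.96.
- With clustering and dropout: 102.07 × 2.96 / 0.67 = 451 (from 103: 103 × 2.96 / 0.67 = 455).
- Stated: 9 × 50 = 450 per arm. The figure reproduces.

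**3. Power on that basis**

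- Completers per practice: 50 × 0.67 = 33.5.
- Effective number per arm: 9 × 33.5 / 2.96 = 101.9.
- Standard error of the difference: 5.1 × √(2 / 101.9) = 0.715.
- Power = Φ(difference / 0.715 − 1.960). For 2 points: Φ(2.80 − 1.96) = 0.799.

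**4. Illustration after the switch**

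The documents give no expected difference after the switch. Suppose the difference is 2 points at six months, the intervention arm holds its gain, and switched controls recover a fraction f of the gap by the end. The residual is then 2 × (1 − f).

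| f (assumed) | Residual difference | Power, design effect 2.96 |
|---|---|---|
| 0 | 2.0 | 80% |
| 0.25 | 1.5 | 56% |
| 0.50 | 1.0 | 29% |
| 0.75 | 0.5 | 10% |

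Applying the design effect to completers instead, 1 + (33.5 − 1) × 0.04 = 2.30, gives 89%, 66%, 36% and 12%. That version does not reproduce 450 per arm (it gives 350 to 354), so the table uses the protocol's own basis. The pattern is the same either way.

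**5. When the six months starts**

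The Abstract counts from the start of the study. The Randomisation section gives a six-month period without saying when it starts for a practice or a patient. Patient recruitment describes a mail-out in which "Patients who do not respond to the first mail-out are sent a reminder letter approximately two weeks later", then further reminders, calls and invitations until 50 patients are enrolled. No accrual length is given. If every patient is to have 12 months within the 15 funded, entry can spread over at most 15 − 12 = 3 months. If the six months runs from study start and entry is staggered, some control patients could reach their own six-month score after the switch. If it runs from each patient's entry, the question does not arise.

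**The case against.** **The end of the study may mean six months.** The phrase is undefined. The year of review is described as a care strategy, the 12-month visit sits under the intervention programme, and a fixed six-month usual-care period suggests a six-month controlled comparison. That may well be the intent. But the same paragraph of the Objectives speaks of an entire year, and data collection runs to 15 months, so a reader cannot get six months from the words used.

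**The model can isolate six months, and details belong in an analysis plan.** A group-by-time model does yield a contrast at each visit, and handling of post-switch data is commonly left to a plan not shown here. Figure 1, also not shown, may mark the comparison point. This stands against any complaint about missing model detail. It does not remove the problem that the article states a time point at odds with its own design. Whatever the figure shows, the Objectives would still need reconciling.

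**Control practices are only invited.** Uptake may be incomplete, which would soften the dilution. But practices that decline are self-selected and do not make up the randomised usual-care arm, and the Abstract says plainly that they switch.

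**Stronger readings to resist.** A reader might infer that the trial cannot answer its question. It can: the randomised six-month contrast exists, and offering controls the intervention later is a legitimate design. A reader might also infer that the six-month comparison is itself contaminated. The documents do not show that: it rests on one phrase in the Abstract, and no accrual length is given.

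**Conclusion.** The point holds as an unreconciled primary time point. As worded, the primary objective asks for a comparison with usual care at a time when usual care is no longer assured in the control arm, and no text shown names the six-month contrast as primary. The contradiction rests on the text alone and needs no numerical assumption.

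The direction of the bias, towards no difference, assumes that the intervention works and that switched controls benefit. Its size cannot be derived from the documents. The fall from 80% power to about 56%, 29% or 10% is illustrative, resting on assumed residuals of 1.5, 1.0 and 0.5 points and a two-sided test. Late exposure of some control patients before their six-month score is only a possibility, conditional on the switch being timed from study start and on staggered entry.

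This should be corrected before analysis, since it decides which result answers the primary question.

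**What to change.** 1. In the Objectives, replace the end-of-study wording with a named comparison: the between-group difference in PHQ-9 change from baseline to six months, using data from before the control practices switch.
2. In the analysis section, identify that contrast as the primary one from the mixed model, and label data after the switch secondary.
3. Reconcile the Abstract with the Randomisation section on whether the six months runs from study start or from each patient's entry, and on whether control practices switch or are invited to.

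The cost is wording only. The sample size stays at 450 per arm, and the planned 80% power for 2 points is kept. The review does not propose a rule for when individual practices switch. Delaying the switch for some practices would shorten their later follow-up within the 15 funded months, and the point does not depend on it.
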